### Sham electroacupuncture

This study has been designed to show the effectiveness and safety of EA, compared to a sham control, on HSP. Therefore, we selected non-penetrating sham needling (Park sham device), which has been developed and validated by previous studies [16, 17] for comparison. The needles will be placed using the Park sham guide tubes exactly at the same 6 acupoints as the verum group and the same electrical stimulators will be connected to the tips of the needles. Since the needles do not penetrate the skin, the stimulation is not electrically conducted. To ensure patient blinded, the low frequency stimulate will be turned on with the same frequency (30 Hz), which makes a fake noise, resulting in the patients believing that they are receiving the real EA therapy for 20 min. The sham group will also complete 9 sessions over a period of 3 weeks (3 sessions a week).

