**Methods:**

After assessing their eligibility, 60 stroke survivors with shoulder pain will be enrolled from two traditional Korean medicine hospitals and randomly divided into either the verum or the sham electroacupuncture (EA) group with a 1:1 ratio. The participants will receive 9 sessions of EA procedures for 3 weeks. The verum EA consists of needling on 6 unilateral acupoints (LI4, LI15, TE14, SI9, SI11, and GB21) with electronic stimulation. A non-penetrating Park sham device and fake electronic stimulation will be used in the sham group on the same acupoints. Patients and outcome assessors will be blinded throughout the entire study. A visual analog scale will be used primarily for the evaluation, and pain rating scale, Fugl-Meyer assessment for upper extremity, modified Ashworth scale, manual muscle test, passive range of motion test, Korean version of a modified Barthel index, and Korean version of the Beck depression inventory will be also be measured. A blinding index will be assessed. For safety, adverse events will be recorded. Data will be statistically analyzed by two-sample t-test or Wilcoxon rank sum test for efficacy and a chi-squared test or Fisher’s exact test for safety, at 5% of significance level.

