### Verum electroacupuncture

The detailed procedures of EA are described following the STRICTA 2010 checklist [12, 13].

The regimen of EA therapy is composed based on the TKM’s theory on acupuncture and the clinical experiences of the TKM experts. All the patients in the verum EA group will go through an identical procedure. On the six adjacent acupoints (LI4, LI15, TE14, SI9, SI11, and GB21), placed on only the side with HSP, the acupuncture needles (stainless steel, 0.25 mm × 40 mm, Dong Bang Acupuncture Inc., Republic of Korea) will be inserted at a depth of 10–15 mm and the de qi sensation will be elicited. Park sham guide tubes will be also used in the verum EA group to blind the patients. The locations of each acupoint conforms to the standard defined by the World Health Organization [15]. Subsequently, a low frequency electronical stimulate (STN-111, Stratek, Republic of Korea) will be connected to the tips of needles to provide electrical stimulation at a medium frequency (30 Hz). Needles with electrical stimulation will be retained for 20 min.

Patients should undergo this procedure 3 times a week for 3 weeks (9 sessions in total). During the procedures, the practitioners are not allowed to talk to patients, minimizing other effects. The practitioners will be licensed TKM doctors with at least 1 year of clinical experience. These practitioners cannot assess the outcomes because assessors should remain blinded throughout the whole study.

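### The sham arm's zero electrical dose rests only on the needles not piercing the skin, which does not by itself stop current from a switched-on stimulator

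*Protocol article*

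**What the plan says.** The Methods paragraph of the Abstract sets the intention: "A non-penetrating Park sham device and fake electronic stimulation will be used in the sham group on the same acupoints". The section "Sham electroacupuncture" then describes how this is done. The needles are held in Park sham guide tubes at the verum points, and "the same electrical stimulators will be connected to the tips of the needles". The device is not left off: "the low frequency stimulate will be turned on with the same frequency (30 Hz), which makes a fake noise", and this continues for 20 minutes per session over nine sessions. One sentence explains why this is meant to deliver nothing: "Since the needles do not penetrate the skin, the stimulation is not electrically conducted".

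The section "Blinding" adds only that an identical stimulator supplies the noise. Nowhere does the article mention a zero output setting, an interrupted lead, an insulating part or an output check.

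**The concern.** Electrical stimulation is what distinguishes electroacupuncture from plain needling, so the comparison with sham depends on the sham arm receiving none. The article energises the sham circuit and relies on the skin surface to block it. If that barrier is incomplete, controls receive part of the active component at the trial's own acupoints. The plan itself treats such stimulation as something to keep out: in "Concomitant treatments", the usual stroke care that is permitted excludes electroacupuncture at these six points.

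If stimulation helps, leakage would pull the difference in VAS change toward zero. A null result could then mean either that the treatment does not work or that the control was partly active. Leakage might also lead sham patients who feel current to guess that they are in the verum group. The blinding index could not tell this apart from a convincing inert sham. Neither problem can be repaired at analysis.

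**Working it through.** **1. The two arms side by side** (sections "Verum electroacupuncture" and "Sham electroacupuncture")

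| Feature | Verum | Sham |
|---|---|---|
| Acupoints | Six, on the painful side | Same six |
| Stimulator attached to needle tips | Yes | Yes, same stimulators |
| Stimulator on, frequency | Yes, 30 Hz | Yes, 30 Hz |
| Time per session, sessions | 20 min, 9 | 20 min, 9 |
| Output intensity | Not stated | Not stated |
| Needle material | Stainless steel | Not stated |
| Insertion | 10–15 mm | None |
| De qi | Elicited | Not mentioned |
| Stated reason for no current | Not applicable | Non-penetration only |

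The electrical set-up as described is the same in both arms. Only insertion and what follows from it differ.

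**2. Does non-penetration imply zero current?** For a circuit with output voltage V and total impedance Z, the current is I = V / Z. It is zero only if V = 0 or the circuit is open (Z infinite). The article states neither. Intact skin has a finite impedance. Not piercing it raises Z and so lowers I at a given V, but lower is not zero. With several connected needles on one side, a return path exists if the needles are conductive and touch the skin. Placement at the acupoints implies contact, though the article does not say so outright.

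**3. Does the cited validation fill the gap?** The article says "we selected non-penetrating sham needling (Park sham device), which has been developed and validated by previous studies". That claim concerns the needling device. The article does not say that it extends to the device wired to an energised stimulator.

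**4. How much exposure rests on the inference?** The number of sham patients comes from "Power calculation", whose figure reproduces:
- difference in VAS reduction: 3.52 − 1.38 = 2.14
- pooled SD: √((2.67² + 2.43²) / 2) = 2.553
- two-sided t-test, alpha 0.05, power 0.80: 23.34, rounded up to 24 per group
- 20% dropout: 24 / 0.80 = 30 per group

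Exposure at full attendance:
- per sham patient: 9 × 20 = 180 minutes
- sham arm: 30 × 9 = 270 sessions
- 270 × 20 / 60 = 90 hours

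This is time connected to a live stimulator, not current delivered, and it would be the same if leakage were nil. The article gives no output, impedance or dose-response figure, so a power loss would rest on an invented shrinkage of the 2.14. None is claimed, and the sample size calculation is unaffected.

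**The case against.** The strongest reply is that harm is conjectural. A current that matters needs a conductive sham needle, skin contact sustained for 20 minutes, a closed circuit, and enough output to stimulate tissue through intact skin. The article establishes none of these. Read practically, the sentence may mean only that no therapeutic stimulation is delivered. Output intensity is missing for the verum arm too, which suggests condensation rather than a gap specific to the sham. The approved full protocol (version 1.5) is not shown and could set the sham output to zero. Stating the frequency does not fix the amplitude. Any bias would be conservative, and insertion and de qi would still separate the arms. Separate sham leads also bring a risk of their own, a verum patient treated with a dead lead.

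Most of this stands as a limit on the claim: leakage is not shown, its size is unknown, and its direction is toward no difference. It does not rescue the sentence. The article does not merely leave the safeguard unmentioned. It gives a reason for zero current, and that reason is wrong as a rule. Non-penetration would not need to be the stated ground if the output were zero or the lead dead. The risk of mixing up leads is real but can be managed by labelling, or avoided with a verified zero-output setting.

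**Conclusion.** The concern holds. As described, the sham procedure does not secure the fake stimulation that the plan intends, because its one stated safeguard does not prevent conduction through skin contact. This should be corrected, but it does not invalidate the design. No estimand, test, error rate or sample size changes.

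The conclusion rests on general physics and on the article's own description of a connected, switched-on stimulator. It does not assume that current flows. The statement about bias toward no difference applies only if leakage occurs and stimulation has some benefit. Even then the contrast would not vanish, since only the verum needles are inserted and, in that arm, "the de qi sensation will be elicited". Confidence is medium, because the full protocol may contain a safeguard that the article does not report.

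**What to change.** In "Sham electroacupuncture", delete the sentence that infers no conduction from non-penetration and state a physical safeguard instead. Either use sham leads with an interrupted circuit, or use an output channel set to zero and verified as dead. In both cases keep the sound and display on so that blinding is unchanged. Check sham leads or channels with a meter before first use and periodically, and record the result. If the full protocol already does this, report it in place of the deleted sentence.

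The cost is a one-off preparation and labelling of leads (or a device setting) at two sites, a short meter check and one amended paragraph. Live and dummy leads must be kept apart so that no verum patient is treated with a dead lead. The verum procedure does not change, and no extra patients or visits are needed.

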### Concomitant treatments

Drugs, such as steroids or nonsteroidal anti-inflammatory drugs, herbal medications, acupuncture, moxibustion, or rehabilitation therapies for shoulder pain in stroke patients are allowed throughout the trial. However, all concomitant treatments for HSP should be maintained with the same dosage and regimen at least 2 weeks before enrollment until the last assessment. If necessary, the participant should take 2 weeks for a run-in period before enrollment. When there are significant changes of concomitant medications in an enrolled participant, he or she will be dropped out.

The typical care for cerebral hemorrhage or infarction, including oral medications (antiplatelet agents, anticoagulants, or neuroprotectants), rehabilitation therapies, traditional herbal medications, acupuncture, moxibustion, and EA therapies except for at the LI4, LI15, TE14, SI9, SI11, and GB21 acupoints will be permitted throughout the study for both groups.

All the treatments that the enrolled patients take will be monitored closely and recorded in case report forms. When any concomitant treatments related to shoulder pain are significantly different between groups, the findings will statistically be adjusted with these data of concomitant treatments.

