### Eligibility criteria

#### Inclusion criteria

We will include any man or woman who a) is 19 years of age or older; b) was diagnosed with cerebral hemorrhage or infarction through an examination using computed tomography (CT) magnetic resonance imaging (MRI) at least 2 weeks prior to the enrollment; c) has hemiplegic shoulder pain with a VAS score ≥ 4; d) agrees that any treatments, including analgesics, for HSP will not be changed from the previous 2 weeks prior to the enrollment until the last evaluation, if applicable; and e) has received a full explanation about the research and has given informed consent.

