#### Exclusion criteria

Participants will be excluded if they have/had a) disorders, traumatic injury, or surgery of shoulders even before their stroke; b) pacemakers, embedded neural stimulator, cardiac arrhythmia, epilepsy, peripheral neural injury on their medical history; c) psychiatric disorders; d) cancer within the past 5 years, regardless of its prognosis and location; e) cognitive impairment that interferes with clinical assessment; f) hypersensitivity to or fear of acupuncture; g) bleeding disorders (e.g. hemophilia or von Willebrand disease, etc.), h) a pregnancy, i) difficulty in communicating with researchers, or j) any other conditions that are considered inappropriate for participating in the trial by experienced practitioners.

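### The limit on outside needling at the six trial acupoints stands only in the stroke-care sentence; stable acupuncture and moxibustion for shoulder pain carry no point limit, so some sham patients may have real needles there

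*Protocol article*

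**What the plan says.** The Concomitant treatments section gives two permissions.

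- **Shoulder-pain care.** The first paragraph lists drugs, herbal medications and needling, and states that "acupuncture, moxibustion, or rehabilitation therapies for shoulder pain in stroke patients are allowed throughout the trial". Its condition is stability: "all concomitant treatments for HSP should be maintained with the same dosage and regimen at least 2 weeks before enrollment until the last assessment". It adds: "If necessary, the participant should take 2 weeks for a run-in period before enrollment". No acupoint is excluded, and EA is not in the list.
- **Stroke care.** The second paragraph begins "The typical care for cerebral hemorrhage or infarction, including oral medications", goes on to rehabilitation, herbal medication, acupuncture and moxibustion, and ends "and EA therapies except for at the LI4, LI15, TE14, SI9, SI11, and GB21 acupoints will be permitted throughout the study for both groups". The six points are named as an exception only here.

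Concomitant treatments are recorded. Adjustment is planned under one condition: "When any concomitant treatments related to shoulder pain are significantly different between groups". The Statistical analysis section likewise makes the covariance analysis depend on a significant difference between groups.

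Under Inclusion criteria, a participant "agrees that any treatments, including analgesics, for HSP will not be changed from the previous 2 weeks prior to the enrollment". Exclusion criteria list "hypersensitivity to or fear of acupuncture" but not current acupuncture. Dropout criterion (e) covers prohibited therapies and refers back to Concomitant treatments for what they are.

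**The concern.** The sham is built on the needle not entering the skin at the same six points where verum patients are needled. The Discussion explains these points as ones proposed for general shoulder pain, so acupuncture given for shoulder pain is the outside care most likely to use them. That is the category with no point limit. Both sites are traditional Korean medicine hospitals recruiting inpatients, so such care is plausible, although the article does not say how common it is.

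Two things are at stake. In an exposed patient the comparison becomes EA plus real needling against sham plus real needling at the same points, which may narrow the contrast. A sham patient who also feels real needles at those points may recognise the sham, and the primary VAS is patient-rated, so this could widen the observed difference instead.

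**Working it through.** **1. Is the gap in the text?**

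| Outside treatment at the six points | Given for shoulder pain | Given as stroke care |
|---|---|---|
| Manual acupuncture, moxibustion | Allowed if regimen unchanged; no point limit | Barred if the exception covers the whole list; allowed if it attaches to EA only |
| EA | Not listed | Barred |

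On either reading of the exception, manual needling at the six points for shoulder pain is open. On the EA-only reading it is open as stroke care too, so the gap is wider. The inclusion, exclusion and dropout criteria do not close it: the first has existing treatment continue, the second does not mention current acupuncture, and the third points back to this section.

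**2. Do the existing safeguards remove it?** The stability rule stops new needling for shoulder pain but keeps needling already in place. Randomization spreads the exposure over the arms without removing it. The adjustment is triggered by a difference between groups, so equal use never triggers it.

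**3. Baseline check of the plan's own figure.** Inputs from Power calculation: reductions of 3.52 (SD 2.67) and 1.38 (SD 2.43), two-sided 0.05, power 0.8.

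- Difference = 3.52 − 1.38 = 2.14 cm.
- Pooled SD = √((2.67² + 2.43²)/2) = 2.553.
- Two-sample t-test (noncentral t): 24 per arm, power 0.811. The normal approximation gives 23.
- 24/0.8 = 30 per arm, 60 in total. The stated figures reproduce.

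**4. Illustration of dilution.** Let p be the share needled at the trial points, equal in both arms, and f the fraction of the contrast lost in those patients. Neither is in the documents. Contrast = 2.14 × (1 − p × f), with the SD held at 2.553.

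| p | f | Contrast (cm) | Power, 24 per arm | Power, 30 per arm | Per arm for 80% |
|---|---|---|---|---|---|
| any | 0 | 2.14 | 0.81 | 0.89 | 24 |
| 10% | 50% | 2.03 | 0.77 | 0.86 | 26 |
| 25% | 25% | 2.01 | 0.76 | 0.85 | 27 |
| 25% | 50% | 1.87 | 0.70 | 0.80 | 31 |
| 50% | 50% | 1.61 | 0.57 | 0.67 | 41 |
| 25% | 100% | 1.61 | 0.57 | 0.67 | 41 |

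**5. Illustration of the opposite direction.** Suppose p = 25%, half to all of the exposed sham patients recognise the sham (12.5% to 25% of the arm), and each reports 1 cm less improvement. The difference is then inflated by 0.125 × 1 = 0.125 cm to 0.25 × 1 = 0.25 cm. With no true effect, the two-sided rejection rate at 24 per arm is 0.053 to 0.063 instead of 0.05. The recognition share and the 1 cm shift are also assumptions.

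**The case against.** The strongest case against is that this is an add-on trial. The Discussion says EA is studied on top of usual therapy, so background acupuncture is intended. If the exception attaches to EA alone, manual needling is treated alike under both labels and there is no inconsistency. EA is absent from the shoulder-pain list, so the tested intervention at the tested points is not expressly allowed under either label. Anyone exposed must have been on an unchanged regimen and still rate pain at 4 or more. Because the endpoint is change from baseline, at least part of the effect of that needling is already in the baseline. The effect sizes have no anchor in the documents. A blinding index is already planned. The full protocol (version 1.5) is not shown and may contain a point-level prohibition.

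Much of this stands, and it sets the limits of the point. Exposure is stable and mostly manual, the dilution may be small, and the figures are illustrations. It does not close the gap. The add-on aim explains allowing background care, but a control defined by non-penetration still loses meaning where real needles go into the same points. The EA-only reading widens the opening. The blinding index can show that blinding failed but does not prevent it. The bar proposed below would not remove every cue either, since stable needling elsewhere on the shoulder continues and patients remember past needling. A stricter rule in the full protocol is possible, but the article as printed states a permission without that limit.

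**Conclusion.** The point holds in a limited form. As written, sham patients already receiving acupuncture for shoulder pain may continue real needling at the six trial points, and neither randomization nor the between-group adjustment deals with equal use in both arms. This weakens the control and may aid recognition of the sham.

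A reader might infer more, and the documents do not support it:

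- **That the trial is underpowered or biased in a known direction.** The illustrations run from no loss at all, through power of 0.57 at 24 per arm, to a slightly inflated difference. They rest on assumed p, f, recognition share and shift, and they do not allow for the part of the effect already in the baseline.
- **That the arms will differ in this care.** Nothing suggests it, and the point does not need it.
- **That patients may start needling for shoulder pain during the trial, or have outside EA at the trial points.** The stability rule excludes the first. The second is not listed for shoulder pain and is barred as stroke care.

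The gap in the text is clear; its practical size is unknown. The change is worth making because it is cheap and extends a limit that the sponsor already set for stroke care.

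**What to change.** In Concomitant treatments, state once that acupuncture, moxibustion and EA at LI4, LI15, TE14, SI9, SI11 and GB21 on the affected side, outside the trial sessions, are not permitted from enrollment to the last assessment, whatever the indication. Ask about such treatment at screening. Patients who receive it stop at the start of the 2-week run-in that the section already provides, so that the two-week stability condition is still met at enrollment. Stable treatment at other points, drugs and rehabilitation stay as they are, and the sample size stays at 60.

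The cost is one sentence and one screening question. Some inpatients would pause needling at six points for about 5 weeks (2 of run-in plus 3 of treatment), and recruitment may slow slightly.

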#### Dropout criteria

Any participant will be dropped from the study if he or she a) has a belated discovery of any ineligible criteria; b) withdraws consent, wants to cease, or refuses to undergo the EA or sham procedures; c) is lost to follow-up; d) shows serious adverse events and fails to maintain the protocol; e) takes concomitant use of the prohibited drugs or therapies (see the section, Concomitant treatments); f) violates the protocol seriously; or g) is considered inappropriate to keep in the trial by investigators’ clinical experience.

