### Outcomes

#### Primary outcome

The VAS is a patient-rated outcome which has been validated for pain [18]. This scale is a 10-cm line where zero represents “not painful at all” and ten represents “most painful.” The patient marks an “x” on the line, based on how intense he/she thinks the pain is, and the assessor measures the length from zero to the “x” mark, which is the pain score. Many clinical trials for poststroke shoulder pain use VAS as their main outcomes [10]. In this study, VAS will be evaluated at every visit and the primary endpoint is defined as the mean change of VAS between the baseline and endpoint to show the intergroup difference. The mean differences of the before and after VAS scores within each group will be subordinately evaluated to see the intragroup effect.

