### Power calculation

The primary endpoint is the mean difference of the VAS scores for poststroke shoulder pain between the baseline and the endpoint. The null hypothesis is that μ_v_ = μ_s_*,* while the alternative hypothesis is *μ*_*v*_ ≠ *μ*_*s*_, where *μ* is the mean difference and *v* and *s* denotes the verum or sham EA group, respectively. A previous study to compare the effectiveness of acupuncture therapy using non-acupoint sham acupuncture on poststroke shoulder pain [29] showed the reductions of VAS scores with means ± standard deviations of 3.52 ± 2.67 in the intervention group and 1.38 ± 2.43 in control group, respectively. Using a two-sided test, under the assumptions of an of 0.05 and (1-β) of 0.8, a sample size of 24 per group has been calculated. Considering a 20% of dropout rate, a total of 60 participants will be enrolled in the trial (30 per group).

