### Statistical analysis

A full analysis set is defined as a group of participants who receive 7 or more verum or sham EA sessions with an evaluation of the primary outcome at the endpoint, while a per protocol set is a subset of participants who complete all verum or sham EA sessions as planned in the protocol. We are going to statistically analyze the obtained data, primarily on the full analysis set, as well as, on the per protocol set for the efficacy analysis. Missing values will be imputed by the method of last observation carried forward in the full analysis set.

Demographic information will be tested with a two-sample t-test or Wilcoxon rank sum test for continuous variables and chi-squared test or Fisher’s exact test for categorical variables. When statistically significant differences between groups are found in demographic information, especially age and sex, those will be used as covariates for effectiveness analysis.

Primary and secondary variables will be summarized using the mean ± standard deviation and tested by two-sample t-test or Wilcoxon rank sum test depending on normality of the distribution. If concomitant treatments are significantly different between groups, intergroup effect will be tested by an analysis of covariance with the information of concomitant treatments adjusted. For the intragroup effect, the results of the VAS scores will be tested by paired t-test or Wilcoxon signed rank test. The significance level will be set at 0.05 (two-sided). Statistical analyses will be performed using SAS® 9.4 software (SAS Institute Inc., North Carolina, USA) by an independent statistician ([name]).

The number of adverse events will be presented with a 95% confidence interval on a safety set defined as a subset of participants who receive at least one verum or sham treatment. A chi-squared test or Fisher’s exact test will be carried out to compare the significant differences between groups.

The results of the blinding assessment will be presented as the number of participants per group assignment with the participants’ deductions of their group assignment in a 2 × 3 table. We will consider blinding to be successful in this study if the calculated confidence interval of the new BI includes zero, following the previous study [14].

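### Participants are dropped from the study after significant changes of concomitant medication or serious violations, and the primary analysis set does not bring them back, so outcome-related loss that differs between arms can bias the VAS comparison

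*Protocol article*

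**What the plan says.** Under Concomitant treatments, shoulder-pain treatment may continue at a constant regimen: "Drugs, such as steroids or nonsteroidal anti-inflammatory drugs, herbal medications, acupuncture, moxibustion, or rehabilitation therapies for shoulder pain in stroke patients are allowed". The consequence of a marked change is removal: "When there are significant changes of concomitant medications in an enrolled participant, he or she will be dropped out".

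The Dropout criteria open with "Any participant will be dropped from the study if he or she". One list then joins withdrawn consent and loss to follow-up with refusal of the procedures, serious adverse events with failure to maintain the protocol, a participant who "takes concomitant use of the prohibited drugs or therapies", one who "violates the protocol seriously", and investigator judgement. Removal is from the study, not only from the procedures.

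Under Primary outcome, "VAS will be evaluated at every visit and the primary endpoint is defined as the mean change of VAS between the baseline and endpoint".

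Under Statistical analysis, the full analysis set, on which efficacy is primarily judged, consists of "participants who receive 7 or more verum or sham EA sessions with an evaluation of the primary outcome at the endpoint". Last observation carried forward applies within that set. The per protocol set is defined by completing all sessions as planned.

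Under Power calculation, dropout is met by enlarging the sample: "Considering a 20% of dropout rate, a total of 60 participants will be enrolled in the trial".

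**The concern.** Entrants have a shoulder-pain VAS of at least 4, and the treatments that must stay constant are treatments for that pain. Poor relief is an obvious reason to change an analgesic, and so is very good relief. A rule that removes people for such a change can therefore select on the primary outcome.

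The analysis section does not repair this. A removed participant without an endpoint VAS is outside the full analysis set, even though earlier VAS values exist. Carrying an observation forward cannot help, because it operates only inside a set that already requires the endpoint VAS. The covariance adjustment for unequal concomitant treatment cannot include people who are no longer in the data. Enlarging the sample for 20% dropout protects precision but does nothing about selection.

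If sham loses more of its poor responders, its mean improves and a real effect shrinks. The reverse pattern inflates the effect.

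**Working it through.** **Inputs (Power calculation).** VAS reduction 3.52 (SD 2.67) for the intervention and 1.38 (SD 2.43) for control; two-sided 0.05; power 0.80; 24 per group; 20% dropout; 30 per group.

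**The plan's figure.** Difference = 3.52 − 1.38 = 2.14. Common SD = √((2.67² + 2.43²)/2) = √6.517 = 2.553. The normal approximation, n = 2(1.960 + 0.842)² × 2.553²/2.14², gives 22.3, so 23. The two-sample t-test has power 0.794 at 23 and 0.811 at 24, so 24 reproduces. 24/0.80 = 30 per group. The allowance is 60 × 0.20 = 12 participants, or 6 per arm.

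**Assumption.** The documents give no dropout rate by cause. I take 6 lost per arm and vary how many are the arm's poorest responders (smallest VAS reduction), with the rest lost at random.

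**Closed-form check.** Removing the lowest fraction q of a normal distribution raises its mean by SD × φ(z_q)/(1 − q). At q = 0.20 the factor is 0.280/0.80 = 0.350. The sham mean rises by 0.350 × 2.43 = 0.85 and the verum mean by 0.350 × 2.67 = 0.93.
- Sham only: 2.14 − 0.85 = 1.29.
- Verum only: 2.14 + 0.93 = 3.07.
- Both arms: 2.14 + 0.93 − 0.85 = 2.22.

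**Simulation at the trial's size** (40,000 trials, 30 per arm, 6 removed per arm, two-sample t-test; separate runs agree to within about 0.01 on the difference):

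| Poorest responders among the 6 lost (sham / verum) | Mean difference | Power |
|---|---|---|
| 0 / 0 | 2.14 | 0.81 |
| 6 / 6 | 2.22 | 0.94 |
| 2 / 1 | 2.01 | 0.82 |
| 1 / 0 | 1.97 | 0.76 |
| 2 / 0 | 1.82 | 0.71 |
| 3 / 0 | 1.69 | 0.66 |
| 6 / 0 | 1.32 | 0.49 |
| 0 / 6 | 3.04 | 0.99 |

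The power of 0.94 in the second row arises because trimming also narrows the SDs.

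**No true effect.** Suppose one arm loses its 6 poorest responders and the other loses 6 at random. With a common SD of 2.43, type I error is about 0.26. With the plan's two SDs it is about 0.24 when sham loses them and 0.29 when verum does.

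**The case against.** Several points on the other side stand.

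- **The end of assessment is inferred.** A reader might take the article to say that no endpoint VAS is obtained after dropout. It does not say so, and the full protocol may provide for follow-up. What the article does state is removal from the study and an analysis set that needs an endpoint VAS. Those two rules are fixed in the text, and together they have the effect described.
- **The triggers are limited.** A reader might infer that any change of pain medication or any breach leads to removal. The text requires significant changes and serious violations, although it defines neither word.
- **The outcome is partly measured.** VAS is taken at every visit, so values exist up to removal. The full analysis set definition is what leaves them unused.
- **Equal loss does little to the difference.** If both arms lose the same number of poor responders, it stays near 2.2. Nothing in the documents shows that loss will be one-sided.
- **The 20% is all-cause.** It also covers withdrawn consent, loss to follow-up and late discovery of ineligibility, so charging all 6 per arm to outcome-driven removal is an extreme. The rows with 1 or 2 such losses are milder.
- **Constant background treatment is a deliberate choice.** Analysing people who changed medication targets a different effect, and that effect may itself be smaller.

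These points limit the size of the concern. They do not remove it, because the design relies on loss being balanced between arms and has no safeguard if it is not.

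**Conclusion.** The concern holds as a design weakness that should be corrected. Followed as written, the plan removes people for reasons that can depend on the primary outcome and then omits them from the primary analysis. The harm depends on differential loss. It ranges from almost none when loss is balanced, through a fall from 2.14 to between 1.97 and 1.82 when one or two sham losses are outcome-driven, to 1.32 at the one-sided extreme or 3.04 in the opposite direction. These are illustrations that rest on 6 losses per arm, normal outcomes and the effect and SDs of the cited study.

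A reader might conclude that the trial will hide a real effect or produce a false one. The documents do not support that: they give no rate of loss by cause or by arm, and the direction of any bias is unknown.

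**What to change.** **Dropout criteria and Concomitant treatments.** Separate stopping or deviating from the assigned procedure from withdrawing consent to data collection. For every reason other than withdrawn consent or loss to follow-up, keep collecting the scheduled VAS, at minimum at the endpoint, and record the deviation and its date.

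**Statistical analysis.** Define the full analysis set as all randomised participants by assigned group, without the 7-session and endpoint-VAS conditions. Add to the per protocol set the exclusion of significant concomitant-treatment changes and serious violations. Its present definition mentions only completed sessions, so once removal ends, a participant who changed medication but completed all nine sessions could enter it.

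**Cost.** Amended wording, and retained assessments within a 3-week schedule for at most about 12 participants, recruited as inpatients. If the effect and SDs were unchanged, analysing 30 rather than 24 per arm would raise power from 0.81 to 0.89. The downside is that the primary estimate then includes the effect of medication changes, which may shrink the difference; the plan should say so. No rule on continuing the procedures or any medication is proposed.
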